### Statistical Plan

2.5

We estimate that the baseline percentage of patients with HF who meet the primary endpoint definition will be ~10% [11]. In the education/notification arm, we anticipate a ~4% absolute improvement to ~14% based on other studies with educational interventions that target patients [11]. Based on our previous experience, we hypothesize that a strategy of a remote, navigator‐led, pharmacist‐driven HF program will increase this proportion to 25% at 3 months after randomization. Our prior pilot study of a similar remote, navigator‐led program formed the basis for this estimate [14]. With 250 patients in each strategy group (500 patients in total) there will be > 85% power to detect a significant difference between groups at a two‐sided 0.05 significance level. We estimate a rate of dropout (patients who stop receiving treatment from the program) of 10%. The primary endpoint (as determined by last observed medication use) will be assessed in all patients.

For the second randomization of the sequence of GDMT therapy initiations in patients with LVEF < 50%, we expect that the percentage of patients in the traditional titration sequencing group who meet the primary endpoint will be 15%. Considering an imbalanced enrollment of patients with HFrEF and HFpEF, with 40% of patients with HFrEF, a total of 100 patients in each group will provide 80% power to detect an 18% difference between groups at a two‐sided 0.05 significance level, with an estimated 10% dropout (patients who stop receiving treatment from the program). This assumption is supported by prior real‐world data demonstrating hyperkalemia rates of approximately 28%–38% with traditional GDMT sequencing, as well as clinical trial data showing that SGLT2 inhibitors reduce the incidence of hyperkalemia and hypotension [20, 21, 22] —two common barriers to the initiation and up‐titration of MRAs and ARNIs [23, 24]. Based on these findings, we believe that initiating therapy with an SGLT2i may mitigate these adverse effects and lead to a higher proportion of patients achieving full GDMT in this arm.

The percentage of subjects who achieve the primary endpoint and other dichotomous secondary outcomes will be compared between the two randomization groups using a two‐sided chi‐squared test. Risk ratios will be calculated as measures of association to express the difference in dichotomous outcomes. Continuous endpoints will be reported as mean and standard deviation or median with the interquartile range depending on the distribution. No adjustment for multiplicity will be made in any of the secondary outcome analyses and, as such, will be interpreted as exploratory.

A planned interim analysis will occur after 100 participants have completed 4 months of the program to evaluate the study progression and operational metrics across the program and will assess if any changes to the study design are needed at that time.

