### Randomization

2.2

Once a patient agrees to participate in the program, they are randomized in a 1:1 manner at the patient level into either (1) the “education‐first” arm (3‐month period of patient and provider education, followed by enrollment in a remote HF medication management program for the optimization of GDMT) or (2) the “simultaneous” arm (parallel participation in patient and provider education and enrollment in a remote HF medication management program for the optimization of GDMT). Education consists of curated print and video microlearning content for patients and providers' notification regarding their eligibility for GDMT before active participation in the remote management GDMT clinic. For patients enrolled with LVEF < 50% not on SGLT2i at baseline, we will perform a secondary randomization to test a strategy of medication titration sequencing using SGLT2i first versus traditional titration sequencing. Traditional titration sequencing is based on approval dates of medications and guideline sequencing and follows the order of BB, ARNI/ACEi/ARB, MRA, and SGLT2i. Patients will be stratified by LVEF (≥ 50% and < 50%) and by enrollment category, either outpatient or post‐hospital discharge (defined as within 30 days of discharge) for prespecified secondary analysis. All randomizations will be completed through computer‐generated algorithms using block randomization with block sizes of 30 without stratifying based on LVEF to ensure an equal number of patients in each group. The randomization allocation based on the blocks will be concealed to the study personnel.

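### The 100 per group planned for the SGLT2i sequencing comparison counts every expected LVEF < 50% enrollee, although only those not on an SGLT2i at baseline are randomised to a sequence

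*Protocol article*

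**What the plan says.** Section 2.5 fixes the overall size: "With 250 patients in each strategy group (500 patients in total"). For the second randomisation it describes the population only as patients with LVEF < 50%, and gives these inputs:

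- Control rate: "we expect that the percentage of patients in the traditional titration sequencing group who meet the primary endpoint will be 15"%.
- Recruitment base, size and power: "with 40% of patients with HFrEF, a total of 100 patients in each group will provide 80% power".
- Effect: "detect an 18% difference between groups at a two‐sided 0.05 significance level".
- Attrition: "with an estimated 10% dropout (patients who stop receiving treatment from the program").

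Section 2.2 defines who enters that randomisation more narrowly. For patients with LVEF < 50% it reads: "not on SGLT2i at baseline, we will perform a secondary randomization to test a strategy of medication titration sequencing".

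Table 1 (section 2.1) excludes an LVEF < 50% patient only when all four classes are prescribed at 50% or more of goal dose, or not tolerated. For LVEF ≥ 50%, being on an SGLT2i is enough to be excluded.

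**The concern.** The two sections describe different populations. Section 2.5 counts all expected LVEF < 50% enrollees; section 2.2 randomises a subset of them. A patient with LVEF < 50% who takes an SGLT2i but lacks an MRA, takes an ACE inhibitor rather than an ARNI, or is below half of goal dose can join the trial but cannot be randomised to a sequence. Section 2.5 makes no deduction for such patients.

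The sequencing question is a named aim in the Introduction and has its own power statement. If fewer patients are randomised than that statement assumes, a reader who takes 80% power at face value may read a non-significant result as evidence that sequence does not matter, when the comparison may have been too small to show an 18-point difference.

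**Working it through.** **Inputs.** p1 = 0.15; p2 = 0.15 + 0.18 = 0.33; two-sided α = 0.05; 10% dropout; N = 500; 40% with LVEF < 50% (all section 2.5). Test: two-sided chi-squared (section 2.5). Restriction to patients not on an SGLT2i at baseline (section 2.2).

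**Step 1: reproduce the plan.** With pooled variance under the null, p̄ = 0.24:

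- √(2p̄(1−p̄)) = √0.3648 = 0.604
- √(p1(1−p1) + p2(1−p2)) = √(0.1275 + 0.2211) = √0.3486 = 0.590
- n = (1.960 × 0.604 + 0.842 × 0.590)² / 0.18² = 87.2, so 88 per group
- with 10% dropout: 88 / 0.9 = 97.8, so 98 per group, against 100 stated

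Power = Φ[(0.18√n − 1.960 × 0.604) / 0.590]. This gives 85.2% at n = 100 and 81.3% at n = 90 (100 less 10%). Exact enumeration of the chi-squared test gives 85.7% and 81.7%. The plan's 80% is reproduced.

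**Step 2: where the 100 comes from.** 0.40 × 500 = 200, and 200 / 2 = 100. Nothing is left over for patients who are not eligible for the second randomisation.

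**Step 3: apply section 2.2.** Let s be the share of LVEF < 50% enrollees already on an SGLT2i. Then n per group = 100(1 − s). The article does not state s, so the values below are assumptions.

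| s (assumed) | n per group, all analysed | Power | n per group, 10% dropout removed | Power |
|---|---|---|---|---|
| 0% | 100 | 85.2% | 90 | 81.3% |
| 10% | 90 | 81.3% | 81 | 77.0% |
| 20% | 80 | 76.5% | 72 | 72.0% |
| 30% | 70 | 70.7% | 63 | 66.1% |
| 40% | 60 | 63.9% | 54 | 59.3% |

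**Step 4: where power drops below 80%.** About 87.2 per group are needed.

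- All randomised patients analysed: 100(1 − s) = 87.2, so s ≈ 13%.
- Dropout removed: 90(1 − s) = 87.2, so s ≈ 3%.

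**Step 5: difference detectable with 80% power.**

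- All analysed: 18.9 points at 20% use (n = 80) and 22.3 at 40% (n = 60).
- Dropout removed: 20.1 points (n = 72) and 23.6 (n = 54).

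**Step 6: what the plan's own baseline figure says about s.** Section 2.5 expects about 10% to meet the primary endpoint at baseline. With LVEF < 50%, meeting it requires an SGLT2i (section 2.4).

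- If the 10% describes the LVEF < 50% stratum, 20 of 200 are ineligible and at most 180 / 2 = 90 per group remain. Power is 81.3%, or 77.0% with dropout removed.
- If it describes all 500 enrollees, that is 50 patients. LVEF ≥ 50% patients on an SGLT2i are excluded, so all 50 fall among the 200, and at most 150 / 2 = 75 per group remain. Power is 73.7%, or 69.1% with dropout removed.

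Both group sizes are upper bounds, because patients on an SGLT2i without all four classes are ineligible too.

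**The case against.** **The power statement is conditional and correct.** It says what 100 per group would deliver, and Step 1 confirms it. This stands: there is no arithmetic error in the power formula. What does not follow from the design is the 100.

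**Dropouts should not be removed.** Section 2.5 defines dropout as stopping treatment from the program and says the primary endpoint, taken from last observed medication use, is assessed in everyone. Section 2.4 sets intention-to-treat for the primary analyses. On that reading the more favourable power column applies, and 10% baseline use still leaves 81.3%. This has weight. However, the sequencing sentence itself includes the 10% dropout, and the article does not say which treatment applies to this comparison, so both columns are shown.

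**The size of the shortfall is unknown.** This also stands. The Introduction's figure of fewer than one in five on an SGLT2i comes from trials in mildly reduced or preserved EF and covers only part of this stratum. A reader might infer from the 10% baseline figure that a quarter of the stratum (50 of 200) is already on an SGLT2i. That needs the 10% to refer to all 500 enrollees. The text says patients with HF and cites a study that the Discussion describes as enrolling patients with HFrEF, so the stratum reading is equally open.

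**The target could still be met.** More than 40% with LVEF < 50%, or more than 500 patients, would make up the loss. The article plans neither.

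**Conclusion.** The point holds as an inconsistency between the sample-size assumption in section 2.5 and the eligibility in section 2.2. On planned enrolment, 100 per sequencing group is an upper bound, and it is missed for any baseline SGLT2i use above zero in the LVEF < 50% stratum.

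A reader might go further and conclude that 80% power is definitely not delivered. The documents do not support that. With all randomised patients analysed, the calculation tolerates about 13% baseline use before power drops below 80%; with dropout removed, about 3%. How far power falls depends on a share that the article does not give and on a dropout rule that it does not settle for this comparison. The results assume 15% versus 33%, equal group sizes, and exactly 200 enrollees with LVEF < 50%. The main comparison of education-first with simultaneous management is not affected.

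**What to change.** Section 2.1 says that enrolment is complete, so the numbers randomised to each sequence can be counted. In section 2.5, or wherever the final analysis is specified:

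1. Replace the 100 per group with the number actually randomised to each sequence, and describe the population as LVEF < 50% and not on an SGLT2i at baseline.
2. Restate the power for 15% versus 33%, or the difference detectable with 80% power, at that number.
3. Say whether patients who stop the program stay in this analysis, and use the same rule in the power statement.
4. Report the sequencing comparison with its confidence interval, so that a non-significant result is not taken as showing no difference.

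There is no need to enrol more patients. The cost is a sentence or two of text and a stated power that is likely to be less favourable.

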**Other efficacy and safety endpoints**			
Process metrics	Number of new GDMT medication classes added	Absolute count of new classes initiated.	6
	Percent reaching maximum tolerated dose	Proportion of patients at maximum tolerated dose for each GDMT class.	6
	Percent on ≥ 50% recommended dose	Proportion of patients on at least 50% of the recommended target dose for each class.	6
	Prescription for four optimal‐dose classes	Proportion of patients with LVEF < 50% who have a prescription for all four GDMT classes at optimal dose.	6
	Utilization of four optimal‐dose classes	Proportion of patients with LVEF < 50% with self‐reported utilization of all four GDMT classes at optimal dose.	6
	Prescription for SGLT2i	Proportion of patients with LVEF ≥ 50% with a prescription for an SGLT2i.	6
	Utilization of SGLT2i	Proportion of patients with LVEF ≥ 50% with self‐reported utilization of an SGLT2i.	6
	Prescription for ARNI/MRA/SGLT2i	Proportion of patients with LVEF 50%–59% with a prescription for ARNI, MRA, and SGLT2i.	6
	Utilization of ARNI/MRA/SGLT2i	Proportion of patients with LVEF 50%–59% with self‐reported utilization of ARNI, MRA, and SGLT2i.	6
	Any worsening HF	Composite of worsening NYHA functional class or hospitalization for HF.	6
Surrogate clinical outcomes	Weight change	Change from baseline (kg).	6
	Blood pressure	Change from baseline (mmHg).	6
	NT‐proBNP	Change from baseline (pg/mL).	6
Clinical outcomes (efficacy and safety)	Any worsening HF	Composite of worsening NYHA functional class or hospitalization for HF.	6
	Hypotension	Systolic blood pressure < 90 mmHg with associated symptoms.	6
	Hypo/hyperkalemia	Serum potassium < 3.0 mmol/L or > 6.0 mmol/L.	6
	Acute kidney injury (AKI)	Increase in serum creatinine by ≥ 1.5 times the baseline value.	6
	Any hospitalization	All‐cause hospitalization.	6
	Death	All‐cause mortality.	6
Health utilization outcomes	Emergency department visit	All‐cause and HF‐specific.	6
	Hospital admission	All‐cause and HF‐specific.	6
	*Patient & provider‐reported outcomes*		
	Patient satisfaction	Net promoter score (NPS) survey.	6
	Provider satisfaction	Assessed via survey.	6
Exploratory outcomes	GDMT medication prescriptions	Analysis of prescription patterns at multiple time points.	1, 2, 6, and 12
	Cost‐effectiveness analysis	Economic analysis of the intervention.	12
	Heart failure collaboratory GDMT score	Change from baseline (for patients with LVEF < 50%).	6

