	Optimization potential score	Change from baseline (for patients with LVEF < 50%).	6

Abbreviations: ACEI, angiotensin‐converting enzyme inhibitor; AKI, acute kidney injury; ARB, angiotensin II receptor blocker; ARNI, angiotensin receptor‐neprilysin inhibitor; BB, beta‐blocker; GDMT, guideline‐directed medical therapy; HF, heart failure; LVEF, left ventricular ejection fraction; MRA, mineralocorticoid receptor antagonist; NPS, Net Promoter Score; NT‐proBNP, N‐terminal pro‐B‐type natriuretic peptide; NYHA, New York Heart Association; SGLT2i, sodium‐glucose cotransporter‐2 inhibitor.

The secondary endpoint is any intensification of GDMT at 3 months, which includes any initiation or titration of a GDMT medication. Intensification of GDMT, which includes any initiation or titration of a GDMT medication, will be captured as the number of intensification steps and compared between treatment groups. For example, the initiation of any dose of an ACEi, followed by two titrations and the initiation of SGLT2i, would count as four intensification steps. We will then compare the primary and secondary outcomes between groups at 6 months postenrollment after all patients receive the remote HF clinic intervention. Patients will be followed actively for 6 months or to the end of active medication management; however, we will continue to obtain data from EHR for another 6 months and compare outcomes at 12 months postenrollment to assess the durability of the results. An interim analysis will be performed after 100 participants have completed 4 months of the program to assess if any changes to the study design are needed based on efficacy, safety, and operational metrics.

The primary analyses will be performed according to the intention‐to‐treat principle, using data for all randomized patients. The “education‐first” group will be compared with the “simultaneous” medication titration and education groups. Sensitivity analyses will be performed in patients engaged in the program for at least 3 months, and in patients who complete the treatment program.

For the second randomization in participants with HFrEF comparing different sequencing of therapies, we will analyze primary and secondary outcomes by comparing patients in the “SGLT2i‐first” and “traditional pathway” GDMT sequencing groups.

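### The sequencing comparison is tested without adjusting for the number of drug classes already in use at entry; adjusting would add a few points of power at almost no cost

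*Protocol article*

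**What the plan says.** Section 2.2 (Randomization) of the protocol article states that, for patients with LVEF < 50% who are not on an SGLT2i at baseline, "we will perform a secondary randomization to test a strategy of medication titration sequencing". Section 2.4 (Outcomes and Follow-Up) says of this comparison that "we will analyze primary and secondary outcomes by comparing patients in the" SGLT2i-first and traditional groups. For LVEF < 50%, the primary endpoint is use of all four classes at any dose at 3 months.

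Section 2.5 (Statistical Plan) gives one method for binary outcomes: the primary endpoint and the other dichotomous outcomes "will be compared between the two randomization groups using a two"-sided chi-squared test, with risk ratios as the measure of association. It names no covariate or stratum. The same section sizes the comparison. It expects that "the percentage of patients in the traditional titration sequencing group who meet the primary endpoint will be 15"%, and that "a total of 100 patients in each group will provide 80% power to detect an 18% difference between groups" at two-sided 0.05, "with an estimated 10% dropout (patients who stop receiving treatment from the program").

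The stratification factors named in section 2.2 are LVEF and enrollment category. The number of classes in use at entry is not among them. Current therapy must nonetheless be known to apply the exclusion criteria in Table 1, and to report two items in Table 2: new classes added ("Absolute count of new classes initiated") and the change from baseline in GDMT score.

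**The concern.** Every patient in the second randomization starts as a non-responder, because the SGLT2i is missing. All are in the same LVEF group, so neither baseline endpoint status nor the LVEF stratum can explain any outcome variation here. What does differ is the distance to the endpoint: someone on three classes needs one start, and someone on none needs four. That distance is built into the endpoint definition, so the baseline count should be prognostic.

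A test that ignores a prognostic baseline variable leaves explainable variation in its standard error. The comparison has its own power calculation, set at 80% with about 100 patients per group. Enrollment is complete, so a more precise analysis is the remaining way to improve it.

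**Working it through.** **Inputs from section 2.5.** Traditional arm 15%; difference 18 points, so 33% in the other arm; two-sided alpha 0.05; 100 per group; 10% dropout, leaving 90 per group if dropouts are lost to the analysis.

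**Step 1: reproduce the stated power.** The mean rate is (0.15 + 0.33)/2 = 0.24. The null term is √(2 × 0.24 × 0.76) = 0.604. The alternative term is √(0.15 × 0.85 + 0.33 × 0.67) = 0.590.

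- n per group = [(1.96 × 0.604 + 0.842 × 0.590)/0.18]² ≈ 87.2, so 88. Dividing by 0.9 gives 98, against 100 stated.
- Power = Φ[(0.18√n − 1.96 × 0.604)/0.590]. At n = 90 this is Φ(0.887) = 81.3%. At n = 100 it is Φ(1.044) = 85.2%.

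The plan's 80% is reproduced for the unadjusted test.

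**Step 2: gain as a function of prognostic strength.** If the baseline count explains a share R² of outcome variance, adjustment multiplies the variance by about (1 − R²). This is equivalent to replacing n by n/(1 − R²). R² is an assumption, since the documents give none.

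| Assumed R² | Power, 90 per group | Gain (points) | Power, 100 per group | Gain (points) |
|---|---|---|---|---|
| 0 | 81.3% | – | 85.2% | – |
| 0.05 | 83.2% | 2.0 | 86.9% | 1.8 |
| 0.10 | 85.2% | 3.9 | 88.7% | 3.5 |
| 0.15 | 87.1% | 5.9 | 90.3% | 5.2 |
| 0.25 | 90.9% | 9.6 | 93.5% | 8.3 |

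At R² = 0.10 the effective size is 90/0.9 = 100 per group, so adjustment would recover the planned dropout loss.

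**Step 3: what R² is plausible?** Assume each missing class is started independently with the same probability s. A patient with k classes missing then succeeds with probability s^k, and R² = Var(s^k)/[m(1 − m)], where m is the overall success rate.

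Example: assume entry on 0, 1, 2 or 3 classes in proportions 0.15, 0.30, 0.35 and 0.20.

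- Traditional arm, s = 0.39: success is 0.023, 0.059, 0.152 and 0.390 by entry count. The mean is about 0.15 and R² = 0.127.
- SGLT2i-first arm, s = 0.60: success is 0.130, 0.216, 0.360 and 0.600. The mean is about 0.33 and R² = 0.112.

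Two sets of calculations used this model:

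- Formula of step 2, with s from 0.35 to 0.55 and three assumed entry distributions: R² = 0.107 to 0.138. Power is 85.4% to 86.7% at 90 per group (about +4 to +5.5 points) and 88.9% to 90.0% at 100 per group (+3.7 to +4.8).
- Simulation of a Cochran–Mantel–Haenszel test stratified on the count, with rates fixed at 15% and 33% and five assumed entry distributions: R² about 0.08 to 0.13. The gain is 2.9 to 4.4 points at 90 per group and 2.5 to 3.5 at 100.

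**Step 4: a different form of association.** With a common odds ratio per class already taken, simulated at 90 per group over four assumed entry distributions, the gain is about 2 points at an odds ratio of 2, 3 to 6.5 at 3, 4.5 to 9 at 4, and 8 to 12 at 6.

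**Step 5: validity.** In a simulation with no effect (24% in both groups, 90 per group), the chi-squared test rejected in 5.0% of runs and the stratified test in 5.1%.

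**The case against.** **Nothing is wrong with the stated test.** This stands. The chi-squared test is valid under randomization and reaches its planned power. A reader might infer that a chance imbalance in baseline count would bias the result. It would not: such imbalance is ordinary sampling error, which the test already allows for.

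**The size of the gain is not in the documents.** This also stands. A reader might infer a loss of 5 to 10 points as a fact of the design. The equal-chance model supports only about 3 to 5.5 points, and the upper end needs about twice the R² of that model. Nor do the documents show that baseline count is the strongest predictor collected. They rank no predictors, and the model has the count explaining only some 10% to 14% of outcome variance. The equal chance of starting each class is itself an assumption; cost, hypotension and hyperkalemia, which the article names as barriers, may act differently by class.

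**The analysed number may be nearer 100 than 90.** This is fair. Section 2.5 defines dropout as stopping treatment from the program, section 2.4 analyses all randomized patients, and the main-comparison paragraph of section 2.5 assesses the endpoint in everyone. Unadjusted power is then about 85% on these inputs and the gain is slightly smaller. It does not vanish.

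**The sequencing analysis may be exploratory, and an unseen SAP may adjust.** The article does not tie the chi-squared test to sequencing by name, and it calls the secondary outcome analyses exploratory. But it names no other test for binary outcomes and gives this comparison its own power calculation, so precision was evidently meant to matter.

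**Conclusion.** The point holds as a cheap improvement in efficiency. The only test stated for the sequencing comparison ignores a baseline value that is already collected and that fixes how many starts each patient still needs.

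On the plan's 15% versus 33%, adjustment would raise power by about 3 to 5.5 points, from 81% at 90 per group or 85% at 100 per group. This rests on an assumed equal chance of starting each missing class and on assumed entry distributions. The gain falls to about 2 points if R² is 0.05 and approaches 10 only if R² is near 0.25. Confidence in any single figure is low. Confidence that the count is prognostic to some degree is higher, because the link follows from the endpoint definition.

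**What to change.** Before the outcome data are analysed, prespecify for the sequencing comparison a logistic model with sequence, number of GDMT classes in use at baseline (0 to 3) and randomized strategy arm, or an analysis stratified on the same factors. Strategy arm belongs in the model because education-first patients enter the remote clinic only at 3 months, which is the primary time point. Report the standardised (marginal) risk difference and risk ratio with 95% confidence intervals, so that the estimand and the risk-ratio scale of section 2.5 are kept. Retain the chi-squared test as a supportive analysis.

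The change needs no extra patients or data. Its costs are a model-based estimate in place of a two-by-two table, and a documented analysis change made after enrollment closed in an open-label trial. The record should therefore show the date of the change and that it preceded any analysis of outcomes by sequence group.
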